## **8.11 PROCEDURES FOR RECORDING AND REPORTING ADVERSE EVENTS**

### **8.11.1 Reporting to sponsor**

Serious adverse events (SAEs) will be reported using a standard SAE reporting form. The investigators will report via e-mail or fax all deaths and immediately life threatening SAEs that occur in the course of the study to the safety monitor and sponsor within 24 hours of the investigational site becoming aware of it to the sponsor.

The PI will report the SAE to Research Ethics Committee (REC) of the College of Medicine, Malawi within 48 hours of being notified. The sponsor will be responsible for reporting AEs and SAEs to the Data Safety Monitoring Board (DSMB) in accordance to a predefined schedule suggested by the DSMB. The sponsor will be responsible for notifying the manufacturer of the investigational product in accordance with the requirements of the manufacturer.

Other supporting documentation of the event may be requested and should be provided as soon as possible. Additional information received for a case (follow-up or corrections to the original case) will be detailed on a *full report* SAE form and emailed to the sponsor within 15 days. This information will be reviewed to consider any action that may be needed in response to reported adverse events.

In case of doubt about whether an event fulfils the criteria for expedited reporting, the case will be reported to the safety monitor who will assess whether the event should be reported in an expedited manner.

All SAEs will be followed until satisfactory resolution or until the Principal Investigator deems the event to be chronic or the patient to be stable.

### **8.11.2 Treatment Stopping Rules**

The investigator will judge whether an adverse event is of sufficient severity to require discontinuation of the study treatment. If this occurs, or if the participant wishes to withdraw due to what he/she considers an intolerable adverse reaction, he/she will be offered an end of study assessment and be given appropriate medical care until symptoms cease or the condition becomes stable. If he/she agrees, he/she will continue to be followed up according to schedule.

The trial may be prematurely discontinued by the Sponsor, Chief Investigator or Regulatory Authority on the basis of new safety information or for other reasons given by the Data Monitoring & Ethics Committee / Trial Steering Committee regulatory authority or ethics committee concerned.

The trial may also be prematurely discontinued due to lack of recruitment or upon advice from a Trial Steering Committee, who will advise on whether to continue or discontinue the study and make a recommendation to the sponsor. If the study is prematurely discontinued, active participants will be informed and no further participant data will be collected.

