## 8.8 PARTICIPANT WITHDRAWAL

Patients can discontinue from the study for any one of the following reasons.

1. Screening error resulting in incorrect enrolment (found that subject did not meet required inclusion / exclusion criteria)
2. Withdrawal of consent at any stage or subject not willing to continue in the study / voluntary discontinuation by the subject
3. Suspected or confirmed allergic reaction to the study drug (removal from therapy only)
4. Safety reasons as judged by the investigator, study safety monitor or DMEC (removal from therapy only)
5. Other

The parents or guardian of subjects who discontinue from the study treatment or from the study entirely will always be asked about the reason(s) for their discontinuation and the presence of adverse events. If a subject discontinues it should be established whether the subject:

1. Discontinues the study treatment, but continues their consent for the data capture up to that point, and to continue follow-up. These subjects will be considered 'off study drug/on study' and where feasible will follow the same schedule of events as those who continue the study intervention, except any adherence assessment. All of these children will be followed until study end at 6 months from enrolment.
2. Discontinues all future activities in the study, but continues their consent for the data captured up to that point to be used in the research
3. Discontinues all future activities in the study and withdraws consent for any data captured to be used for the research

Every effort will be made to follow-up patients who discontinue due to drug related adverse events in order to determine the final outcome. If a subject discontinues due to drug-related adverse events, all the assessments will be conducted that would have been carried out at the next scheduled visit at 6 month (unless consent is withdrawn). This will be recorded in the Case Record Forms (CRFs). The study drug will be returned by the subject. Subjects that have discontinued the study prematurely will not be replaced.

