### 8.10 EXPECTED DURATION OF TRIAL

The total duration of the trial for a participating mother/guardian-child pair is 3.5 months. Participant recruitment will occur for 30 months. There will be 4 months of follow-up of the last recruited subject and finally 6 months to complete data analysis and study reporting. The end of trial will be defined as the final assessment of the last participant within the trial, unless additional time is needed for follow-up of a trial-associated adverse event. This new protocol is a continuation of COMREC study P.02/15/1679.

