### **14.6 Ancillary and post-trial care**

#### **14.6.1 Health care during the trial**

All care directly related to the proper and safe conduct of the trial, and the treatment of immediate adverse events related to trial procedures will be provided free of charge by the local hospitals. The provision of ancillary care beyond that immediately required for conduct of the trial will not be covered by the trial. The use of a health passport or national equivalent will aid the identification of study children.

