#### 20.2.2.6 Trial Reports and actions TSC meeting

The TSC shall provide at each meeting a summary report of their findings and recommendations which must be submitted to the funder, the Sponsor and the TMG.

If the TSC makes a recommendation that the trial should be stopped or suspended, the Sponsor will take the necessary action to ensure that new recruitment to the trial is stopped whilst the TSC report is evaluated and the Research Ethics Committee is informed.

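### Section 8.11.2 ends all participant data collection on any early stop, so the protocol has no provision for collecting new safety events after a stop for safety

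*Protocol*

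**What the plan says.** Section 8.11.2 deals with stopping at two levels.

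- **One child.** A child whose treatment is stopped for an adverse event is offered an end-of-study assessment and care. "If he/she agrees, he/she will continue to be followed up according to schedule".
- **The whole trial.** The sponsor, chief investigator or regulator may end the trial early "on the basis of new safety information" or for other reasons given by the oversight bodies. It may also end for poor recruitment or on steering committee advice. The section then closes: "If the study is prematurely discontinued, active participants will be informed and no further participant data will be collected". No exception is given for a stop on safety grounds.

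Other sections bear on the same situation:

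- Section 8.11.1: "All SAEs will be followed until satisfactory resolution or until the Principal Investigator deems the event to be chronic", or the patient to be stable.
- Section 8.10: the end of trial is the last participant's final assessment, "unless additional time is needed for follow-up of a trial-associated adverse event".
- Section 8.8, on children who stop because of the drug: "Every effort will be made to follow-up patients who discontinue due to drug related adverse events in order to determine the final outcome". The same section lists a DMEC safety judgement as a ground for removing a child from therapy only, with follow-up continuing if consent is kept.
- Section 20.2.2.6: if the steering committee recommends stopping, "new recruitment to the trial is stopped whilst the TSC report is evaluated".

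**The concern.** A stop for safety is the situation in which later events in recently dosed children are most informative. The protocol names dose-dependent QTc prolongation as the main concern with piperaquine and describes the drug as having a long half-life (Section 14.5.4), so exposure outlasts the last dose. The written rule ends data collection at that moment, for every child still in follow-up.

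The rule also gives a trial-wide safety stop weaker follow-up than one child's withdrawal. A single child taken off DHP is followed to schedule if the carer agrees; when the whole trial stops for safety, the text provides for no one to be followed.

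At stake is the evidence that the sponsor and the DMEC would have for judging the signal. The comparison of arms under specific objective 3 (Section 7.2) is a lesser matter, because every arm receives DHP and all arms are cut off alike.

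**Working it through.** The protocol gives no figure for this point, so the check is first one of text and then an illustration of scale.

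**Text.** The question is whether any provision covers a *new* event, after a trial-wide stop, in a child already given DHP.

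| Section | What it covers | Collects new events after a trial-wide stop? |
|---|---|---|
| 8.11.1 | SAEs followed to resolution; expedited reports for events during the study | No. It fits SAEs already known, and read literally it conflicts with 8.11.2 |
| 8.10 | Extra time to follow a trial-associated event | No. It does not provide for detecting further ones |
| 8.8 and first paragraph of 8.11.2 | Children taken off drug individually, including by DMEC judgement | No. Individual level only |
| 20.2.2.6 | Pause in recruitment while a recommendation is evaluated | No. Silent on follow-up after closure |
| 14.2 and 17.2 | Compliance with local SAE reporting rules; safety reports to the manufacturer | No. Duties to report, with no contact or surveillance to find events |
| 14.6.1 | Free treatment of trial-related events | No. Care, not recording |

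**Scale.** Inputs: 375 children (Section 8.3), 30 months of recruitment (Section 8.10), first DHP course at week 2, end visit at 14 weeks (Table 2) or 15 weeks (Section 8.12.5). Assumed, not stated: even accrual, on-time dosing, no dropout, 30.44 days per month.

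1. Accrual: 375 / 30 = 12.5 children per month.
2. Past the first due date and still in follow-up on a given stop date, once recruitment has run at least 14 to 15 weeks:
   - 14-week end: 12.5 × 84 / 30.44 = 34.5
   - 15-week end: 12.5 × 91 / 30.44 = 37.4
   - with accrual 25% slower or faster: 34.5 × 0.75 = 25.9 to 37.4 × 1.25 = 46.7
3. Mean follow-up left: 12 / 2 = 6 weeks, or 13 / 2 = 6.5 weeks.
4. Child-weeks left: 34.5 × 6 = 207; 37.4 × 6.5 = 243.
5. Background events. Section 6.1 gives 8% dead and a further 8% readmitted with severe anaemia by 6 months in Malawi, 16% together. Taken as constant over 26 weeks:
   - 207 × 0.16 / 26 = 1.27
   - 243 × 0.16 / 26 = 1.49
   - with the 31% reduction reported for chemoprevention in Section 6: 207 × 0.16 × 0.69 / 26 = 0.88
6. If the 26-week passive surveillance in Table 2 is the true horizon: 12.5 × 168 / 30.44 = 69.0 children, × 12 weeks = 828 child-weeks, × 0.16 / 26 = 5.1 events.
7. Children in Arms 1 to 3 (three-fifths of accrual) past the first due date with a course still to give at home, weeks 2 to 10: 12.5 × 0.6 × 56 / 30.44 = 13.8.

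**The case against.** The strongest reply is that the protocol already has routes that avoid the harm.

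- **Therapy can be stopped without stopping the study.** Section 8.8 lets the DMEC take children off drug for safety and keep them under follow-up. This is true, but the provision is written for individual children and does not govern a discontinued trial.
- **Stopping is staged.** A steering committee recommendation first pauses recruitment only, and the DMEC may recommend a protocol change instead (Section 20.2.3.3). This stands as a limit: the rule bites only after a final decision, by which time some of the remaining follow-up may already be complete. The child-weeks above are therefore those left at the moment of final closure.
- **Reporting duties remain.** Sections 14.2 and 17.2 are not confined to an open trial. A reader might infer that events after the stop would certainly go unrecorded; the documents do not support that, because sites may still learn of events and report them. What is missing is planned collection.
- **The sentence may be loose drafting.** It closes the paragraph on recruitment and committee advice, not the one on safety. Yet it is worded for any premature discontinuation, and committee advice may itself rest on safety.
- **The numbers are small and uncontrolled.** One or two background events, with no arm free of DHP, add little beyond single-case review. This also stands, although case review is much of what a safety assessment after closure consists of.

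Other stronger readings also fail. Children do not lose care: "the treatment of immediate adverse events related to trial procedures will be provided free of charge by the local hospitals". Open SAEs need not be abandoned, since Sections 8.10 and 8.11.1 can be read as still applying. Nor does Uganda's 36.5% in Section 6.1 give an upper bound for the figures above: 243 × 0.365 / 26 = 3.4 counts death or any readmission, a broader event.

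**Conclusion.** The point holds in a limited form. Section 8.11.2 states an unconditional rule that conflicts on its face with the follow-up of open SAEs, reverses the protection given to a single child, and leaves the protocol with no means of collecting new safety events after a trial-wide stop for safety. This is something the protocol states, not a detail left to a later document.

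It arises only if the trial is finally stopped early. A completed trial and its primary outcome are unaffected. The scale is about 34 to 37 children past their first DHP due date and 207 to 243 child-weeks, or roughly 1.3 to 1.5 background deaths or severe-anaemia readmissions. That rests on even accrual, on-time dosing, no dropout, a 14- to 15-week end visit and a constant rate. It falls to about 0.9 if chemoprevention works as in the earlier Malawi trial, and would be about 5 if 26-week surveillance applies. Section 6.1 puts particular risk in the first 3 months, so a constant rate probably understates the count. These are background events, not events attributed to DHP.

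The amendment is worth making because it is cheap and the present wording is wrong for the case where it matters most.

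**What to change.** Replace the last sentence of Section 8.11.2 with wording to this effect:

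*On any premature discontinuation, carers of children still in the study will be told, and open SAEs will be followed as set out in 8.11.1. Where the reason is safety, vital status, hospital admissions and AEs/SAEs will continue to be collected, subject to consent, for all enrolled children to their planned end visit. Carers holding DHP at home will be told whether to stop dosing.*

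Return of unused drug is already required by Section 8.6.4.4 and need not be repeated. For stops unrelated to safety, the cross-reference to 8.11.1 is enough.

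The cost is a short amendment. If a safety stop occurs, some staff and transport must be kept on for up to about 15 weeks after closure, for contacts and passive surveillance that are already planned. Apart from finishing the follow-up of open SAEs that 8.11.1 already requires, a stop for other reasons adds nothing.

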## 8.12 PARTICIPANTS TIMELINE

### 8.12.1 Overview Study Phases

The study plan and schedule of assessment is provided Table 2: Study Design and Schedule of Assessment.

It consists of an in-patient pre-study screening period while the patient is acutely ill (approximately -4 to 0 days before enrolment) followed by a screening and enrolment at discharge. It will be during this enrolment visit when the children become formal study participants ( $t=0$ ). They will also be provided with artemether-lumefantrine (AL) (Coartem®) during the time they in hospital.. During enrolment visit (at discharge), the child will be allocated to one of the 5 study arms. Depending on the arm the mother and child will either return to OPD clinic for PMC drugs at 2, 6 and 10 weeks or be given at discharge to administer them at home also at 2, 6 and 10 weeks. The subjects (a subset) will be visited again at home at 2, 6 and 10 weeks after enrolment to assess DHA uptake for each PMC treatment course. These home visits will be for adherence check purposes, vital registration and health economic assessments only, not for clinical assessment. The PMC period ends at 14 weeks, i.e. 4 weeks after the third PMC course. They will then be requested to come to the clinic at 15 weeks after enrolment for an end of study assessment. Subject's parent or guardian will be instructed to return his/her child to the study clinic for evaluation free of charge at any time their condition warrants medical attention during the 14 weeks follow-up period after discharge.

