| Location                    | In-Hospital             |                               |                                  | Clinic                    | Home/OPD                                               |                                     |                                      |                          |          |          |           |           |           | Clinic            |
| Visit number                | Pre-study Screening     | Screening Consent & Base-line | #1
t=0 weeks;
Allocation   | #2
t=2 weeks;
DHP 1 | #3
t=6 weeks
DHP 2                               | #4
t=10 weeks
DHP 3           | #5
Study end visit                | 14 wks
(day 98 +/- 7) |          |          |           |           |           |                   |
| Visit description           |                         |                               |                                  |                           |                                                        |                                     |                                      |                          |          |          |           |           |           |                   |
| Study Time                  |                         |                               |                                  |                           |                                                        |                                     |                                      |                          |          |          |           |           |           |                   |
|                             | Days -4 a -0 | Day0                          |                                  |                           | 2 weeks (day 14 +/- 3) c                    | 6 weeks (day 42 +/- 4) c | 10 weeks (day 70 +/- 4) c |                          |          |          |           |           |           |                   |
|                             |                         |                               |                                  |                           | 2w- Day 1                                              | 2w- Day2                            | 2w- Day3                             | 6w- Day1                 | 6w- Day2 | 6w- Day3 | 10w- Day1 | 10w- Day2 | 10w- Day3 |                   |

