|                                            |                         |                               |                       |                                                                                                                                                                           | X        | X        | X                    |          | X        | X                       | X         |           |                       |
| Patient costs                              |                         |                               | X                     |                                                                                                                                                                           |          |          |                      |          |          |                         |           |           | X                     |

Visit #1: Enrolment and randomisation at discharge

Visit #2 #3#4: Home visits at 6, 10 and 14 weeks after enrolment to assess uptake of the 1st, 2nd and 3rd treatment course of the PMC study drugs respectively.

Visit #5: at 3.5 months after enrolment. This is the close out assessment.

---

- a. Children can be pre-study screened any time between hospital admission and enrolment. The figure of -4 days is provided for illustration purposes only.
- b. Visit window= number of days an actual subject visit may fall outside of the planned protocol schedule visit to still meet protocol requirements. DP should be given at least 4 weeks apart.
- c. MS, malaria smear. This will be collected for research purposes only, and read days to weeks later. Malaria smears will not be used for point of care. If participants are symptomatic (e.g. fever) an RDT will be taken for point of care.
- d. VP=vena puncture. FP=finger prick, DP=dihydroartemisinin-piperaquine, , Hb=haemoglobin, MS=malaria smear, Pf=Plasmodium falciparum

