#### 8.7.4.5 Location of household and issuance of study ID card

A detailed route description to locate the household of the participant including sketching of a map will be taken, to aid the planned spot checks to assess uptake of PMC at home. Lastly a subject's identification card will be issued. A GPS will be used to collect the exact location of the participant's house.

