## 8.9 OUTCOMES

### 8.9.1 Primary Outcome

The primary outcome is the 100% of PMC drugs uptake (defined as administration of **all** 3-day treatment courses, given 2, 6 and 10 weeks after discharge) assessed by unannounced spot checks.

The PMC uptake will be assessed through a study questionnaire administered at unannounced spot checks to determine if and when children and their mothers/guardians attend the scheduled dosing of the drug. The spot checks will be conducted at day 4 or 5

of each DHP treatment course. The effectiveness of the delivery mechanism will be determined by the following measures:

1. **Pill count:** Research Assistants will perform a pill count of the drugs available at the day of the visit. This will be used to assess whether participants took the whole course of DHP or not.
2. **Interview:** A face-to-face interview with the mothers/guardians of children participating in the study will be done to collect information on missed doses and possible reasons for any missed doses.

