#### 8.12.4 1st, 2nd and 3rd PMC treatment schedules

The 1st, 2nd and 3rd PMC treatment will be given 2, 6 and 10 weeks following enrolment. These treatments will be given at home for those randomised to Arm 1, 2 or 3 and at OPD for those randomised to Arm 3 and 4 (Day 1 dose only, Day 2 and 3 will be at home). PMC uptake will be assessed by unannounced visits on day 4 or 5 after each treatment course by a research assistant. If children are found to be ill during these home-visits they will be referred to the study clinic for further evaluations as part of the unscheduled visits as described below.

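### The protocol contradicts itself on which children are checked for the primary outcome and on when the check takes place

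*Protocol*

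**What the plan says.** Sections 7.3.1 and 8.9.1 define the primary outcome as administration of all three "treatment courses, given 2, 6 and 10 weeks after discharge) assessed by unannounced spot checks". Section 8.9.1 measures it by a pill count on the day of the visit and an interview about missed doses.

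**Who is checked.** The overview in 8.12.1 says: "The subjects (a subset) will be visited again at home at 2, 6 and 10 weeks after enrolment to assess DHA uptake". Section 8.12.4 has no such limit: "PMC uptake will be assessed by unannounced visits on day 4 or 5 after each treatment course by a research assistant". Section 8.7.4.5 records each participant's household location, also without a limit, "to aid the planned spot checks to assess uptake of PMC at home". Section 8.3 sizes the trial at 25 clusters of 3, so 75 children per arm and 375 in all, with 10% loss to follow-up.

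**When.** Four statements are given:
- 8.12.1: weeks 2, 6 and 10.
- Notes to Table 2 (section 4.2): "Home visits at 6, 10 and 14 weeks after enrolment to assess uptake".
- 8.9.1: "The spot checks will be conducted at day 4 or 5" *of* each course.
- 8.12.4: day 4 or 5 *after* each course.

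Table 2 itself heads visits 2 to 4 with weeks 2, 6 and 10, starting at "2 weeks (day 14 +/- 3"), so it disagrees with its own notes. It also marks uptake on every dosing day.

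**The concern.** A binary endpoint that needs all nine daily doses depends on when, and in whom, the count is made. Field staff who follow 8.12.1 to the letter would leave some children without a primary outcome, in an open-label trial and with no rule for choosing them. They would also call at the nominal dosing weeks, when a three-day course may not be finished. Staff who follow the Table 2 notes would call about four weeks later and rely on recall. These are different measurements of the same endpoint. The protocol does not say which applies, whether the day is counted from the scheduled or the actual first dose, or how a course still in progress at the check is scored.

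**Working it through.** **1. The plan's own figure.** Inputs from 8.3: 50% v 75%, alpha 0.05 (two-sided assumed), power 80%, ICC 0.1, mean cluster size 3, CV 0.19, loss 10%.

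- Design effect = 1 + ((1 + CV²)m − 1) × ICC = 1 + (1.0361 × 3 − 1) × 0.1 = 1.211.
- Unpooled n = (1.960 + 0.842)² × (0.25 + 0.1875) / 0.25² = 54.9 per arm.
- 54.9 × 1.211 / 0.9 = 73.9, or 24.6 clusters of 3, rounded up to 25 clusters = 75. The figure reproduces.
- Power at 75 per arm: 75 × 0.9 = 67.5 evaluable; 67.5 / 1.211 = 55.7 effective. Power is 81% (unpooled variance) or 79% (pooled).

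**2. If only a fraction f is visited.** The protocol gives no f, so the fractions below are assumptions. Evaluable n = 67.5f. Either whole villages drop out (design effect stays 1.211) or fewer children are taken per village (m becomes 3f, with a design effect of 1.133 at f = 0.75, 1.055 at 0.50, and 1 at 0.25). Power is pooled / unpooled:

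| f | Evaluable per arm | Fewer villages | Fewer children per village |
|---|---|---|---|
| 1.00 | 67.5 | 79% / 81% | 79% / 81% |
| 0.75 | 50.6 | 66% / 69% | 69% / 71% |
| 0.50 | 33.8 | 49% / 51% | 54% / 57% |
| 0.25 | 16.9 | 27% / 29% | 32% / 34% |

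**3. Timing.** The windows in the first part of Table 2 are day 14 ± 3, 42 ± 4 and 70 ± 4. (Its continuation prints the week-14 window against week 6; the first part is used here.) I take the window to govern the start of the course. The latest in-window third dose is then day 17 + 2 = 19, 46 + 2 = 48 and 74 + 2 = 76.

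| Reading | Check days, courses 1 / 2 / 3 | In-window courses unfinished at the check |
|---|---|---|
| 8.12.1, weeks 2, 6, 10 taken literally | 14 / 42 / 70 | Even an on-time start |
| 8.9.1, day 4-5 of the scheduled course | 17-18 / 45-46 / 73-74 | Starts two or more days late; one day late if checked on day 4 |
| 8.12.4, day 4-5 after the scheduled last dose | 20-21 / 48-49 / 76-77 | Only a start 4 days late in course 2 or 3, checked on day 48 or 76 |
| Table 2 notes, weeks 6, 10, 14 | 42 / 70 / 98 | None, but 26 days after an on-time last dose |
| 8.9.1, day 4-5 of the actual course | Varies by child | None |

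The notes to Table 2 also require courses at least 4 weeks apart. A first course started on day 17 therefore moves the second to day 45 or later and the third to day 73 or later, so one late start carries over to later checks.

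**The case against.** The subset rests on one parenthesis in an overview paragraph. Every passage that defines the outcome or sets out its procedure is unrestricted, and household locations are recorded for all. The same paragraph says that the home visits also serve the health-economic assessment, and 8.1.2 runs the economic sub-study in a subset, so the parenthesis may simply be misplaced. This stands: a reader might infer that the endpoint is in fact collected in only part of the sample, but the documents show a contradiction, not a settled design.

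The power loss also applies to the pairwise comparison that 8.3 sizes. For the SMS main effect with arms combined (150 v 150, same assumptions, pooled variance), power would be 98% with everyone visited and still 79% with half.

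On timing, a reader might infer that late but valid courses are scored as missed, and that this inflates the apparent effect of reminders. The documents do not support either step. No scoring rule is given. The first step needs the *of* reading, a scheduled-dose anchor and a pill count that is final, although 8.9.1 adds an interview; under 8.12.4 the problem almost vanishes. Section 8.6.3, on forgotten doses, concerns the set time of day and says nothing about starting a course days late. Nothing in the protocol shows how late starts would differ by arm. If timeliness belongs to the outcome, as the wording in 11.7.4 on receipt to schedule may imply, earlier dosing after a reminder is a real effect.

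An anchor on the actual first dose would remove the timing problem, but the protocol describes no means of knowing that date before an unannounced visit in the three home arms. The OPD arms have a dated dispensing log (8.6.4.5).

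**Conclusion.** The point holds as a contradiction that has to be resolved, because it concerns who has the primary endpoint and when it is measured. Followed literally, 8.12.1 leaves part of the powered sample without the outcome and checks before an on-time course need be complete. The loss of power cannot be fixed from the protocol. With assumed coverage of 75% or 50%, pairwise power is about 66-71% or 49-57%, against the stated 80%; with full coverage the stated figure stands.

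The effect of timing depends on which statement applies: substantial under 8.12.1 read literally, confined to starts one or more days late under day 4-5 of the scheduled course, and almost nil under 8.12.4. No size can be put on misclassification or on a difference between arms, because the documents give neither a scoring rule nor a distribution of start dates.

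**What to change.** - In 8.12.1, delete the subset parenthesis and state that every enrolled child has all three uptake checks. If a subset is intended, give its size and selection rule and restate the power in 8.3.
- Give one visit time and its anchor (scheduled or actual first dose) in Table 2 and its notes, 8.9.1, 8.12.1 and 8.12.4. Set it after an in-window course can be finished, for example from days 20, 49 and 77.
- Alternatively, keep day 4 or 5 and re-count any in-window course that is unfinished at the next visit before scoring it as failed.
- State how an in-window course that is unfinished at the check is scored.

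The windows and the dosing schedule need no change. If all children were always meant to be visited, the cost is protocol and SOP wording plus a check a few days later with slightly longer recall. If a subset was really planned, visiting everyone adds field visits.
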